## Abstract

**Background:**

Oropharyngeal administration of colostrum (OAC) has an immune-stimulating effect on oropharyngeal-associated lymphoid tissue, and can promote the maturation of the gastrointestinal tract. However, how OAC promotes intestinal maturation in preterm infants by altering gut microbiota remains unclear. We aim to assess changes in gut microbiota and metabolites after OAC in very preterm infants.

**Methods:**

A multicenter, double-blind, randomized controlled trial will be conducted in three large neonatal intensive care units in Shenzhen, China, with preterm infants with gestational age less than 32 weeks at birth and birth weight less than 1500 g. It is estimated that 320 preterm infants will be enrolled in this study within one year. The intervention group will receive oropharyngeal administration of 0.2 ml colostrum every 3 h, starting between the first 48 to 72 h and continued for 5 consecutive days. Following a similar administration scheme, the control group will receive oropharyngeal administration of sterile water. Stool samples will be collected at the first defecation, as well as on the 7th, 14th, 21st and 28th days after birth for analysis of effect of OAC on gut microbiota and metabolites through 16sRNA gene sequencing and liquid chromatography-mass spectrometry.

**Discussion:**

This proposal advocates for the promotion of OAC as a safe and relatively beneficial protocol in neonatal intensive care units, which may contribute to the establishment of a dominant intestinal flora. Findings of this study may help improve the health outcomes of preterm infants by establishment of targeted gut microbiota in future studies.

**Trial registration:**

NCT05481866 (registered July 30, 2022 on ClinicalTrials.gov).

## Background

Human milk can improve the health outcomes of preterm infants and reduce the risk of necrotizing enterocolitis (NEC) and late onset sepsis (LOS) in early life [1]. This is because of bioactive components tin beneficial breast milk [2], especially colostrum, which expresses essential biological factors such as fatty acids, hormones, immunoglobulin, lactoferrin and oligosaccharides [3–5]. These beneficial biological factors in colostrum also seem to have a unique preventive effect on allergic diseases and chronic diseases later life [6, 7].

Early colostrum feeding can have many benefits for preterm infants. However, some very low birth weight infants often exhibit unstable clinical symptoms such as unstable breathing, poor sucking and poor gastrointestinal function shortly after birth. Therefore, fasting or the slow progress of enteral feeding is a common clinical manifestation of preterm infants [8]. Thus, these preterm infants do not receive all protective biological factors provided by human milk in the early stage of life. In addition, even though some preterm infants can be fed with human milk at an early stage, they need nasal feeding instead of direct oral feeding because of uncoordinated sucking and swallowing function [9]. This prevents establishment of protective biological factors in the oropharynx of very preterm infants within the first few weeks of life, predisposing them to many diseases in early life [10].

Oropharyngeal administration of colostrum (OAC) can be used as a natural alternative administration technique. In OAC, a small amount of colostrum rich in biological factors is injected into the surface of oral mucosa to stimulate an immunostimulatory effect on the infant's oropharyngeal-associated lymphoid tissue [11, 12], including promoting the absorption of secretory immunoglobulin A and lactoferrin [13]. In addition, it can promote gastrointestinal immune function and systemic anti-infection ability, thereby promoting the maturation of the gastrointestinal tract [14, 15].

An optimized human gut microbiota composition is one of the signs of optimal maturation of the gastrointestinal tract and plays a key role in regulating the health and disease risk in preterm infants [16, 17]. With recent advances in high-throughput multiomics technology, including metagenomics and metabonomics, as well as the measurement of host diseases and microbiota, many bacteria and bacterial products causing human diseases (such as inflammatory bowel disease and type 2 diabetes) have been identified [18]. Many intestinal microorganisms and metabolites are involved in the pathogenesis of LOS and NEC in preterm infants [19, 20]. Although LOS pathogens are diverse (including Staphylococci and Enterobacteriaceae and obligate anaerobes), they are typically enriched a few days before the onset of the disease and produce unique metabolites (such as ethanol and formic acid) [21, 22].

Before diagnosis of NEC, notable differences in enrichment of gut microbiota occur. The gut becomes enriched with Proteobacteria dominated by Enterobacteriaceae, whereas Firmicutes, dominated by Staphylococcus, is relatively lacking. As a result, there is excessive growth of pathogenic bacteria under specific conditions and the reduction of biodiversity. Microbiome optimization may provide a new strategy for the prevention of NEC [23, 24]. In addition, studies have explored preclinical diagnostic value of fecal metabolites (such as short chain fatty acids, including acetate and butyrate) for NEC [25, 26].

Although evidence is inadequate and the mechanism is not clear, gut microbiota and metabolites are potentially useful as biomarkers for early diagnosis of NEC and LOS [27]. Therefore, it is beneficial to identify customized mode of intestinal microorganisms and the biological mechanism underlying metabolite changes before NEC and LOS onset [28, 29].

The microbiome-metabolome association is bidirectional [30]. Host and gut microbiota interact through either symbiosis or imbalance of small molecule metabolites. Metabonomics is undoubtedly a promising method to study the interaction between host and gut microbiota [31]. Metabolites of bacteria may also be novel therapeutic targets for human chronic diseases [32]. Several previous studies have investigated the effect of OAC on enteral feeding, NEC, LOS, mortality, etc. [33–39]. Because of limited sample size and inconsistent OAC measures, among other reasons, there is no sufficient evidence to prove that OAC can reduce the incidence of NEC, LOS and death [40]. But OAC can promote intestinal maturation and rapidly achieve total enteral feeding [41, 42]. However, the mechanism by which OAC promotes intestinal maturation by changing intestinal microbiota and metabolites remains elusive, which is the significant contribution of our study.

We hypothesized that OAC could promote relative enrichment of intestinal Firmicutes but reduce relative enrichment of Proteobacteria. In addition, the production of short chain fatty acids and other metabolites would change accordingly to resemble the gut microbiota profile in normal full-term breast fed infants, improving the health outcomes of preterm infants. The purpose of this multicenter, double-blind, randomized controlled trial is to evaluate whether OAC can modulate gut microbiota diversity and metabolites (such as short chain fatty acids) compared with oral care with sterile water.

## Methods

This study is based on the standard protocol items: recommendations for interactive trials (SPIRIT) [43].

### Study design

This multicenter, double-blind, randomized controlled trial will be conducted in three large neonatal intensive care units (NICUs) in Shenzhen, Guangdong Province, China, from October 1, 2022 to September 31, 2023. The purpose of this study is to evaluate the effect of OAC on gut microbiota and metabolites. Preterm infants with gestational age < 32 weeks and weight < 1500 g will be evaluated. Infants who meet these inclusion criteria will be randomly divided into two groups in a ratio of 1:1. The intervention group and control group will receive 0.2 ml oropharyngeal colostrum and 0.2 ml sterile water, respectively, every three hours for five days. Stool samples will be collected at the first defecation, as well as on the 7th, 14th, 21st and 28th days to detect the gut microbiota and metabolites. A flow diagram of the research process including the planned study phases is shown in Fig. 1.

**Fig. 1 Fig1:**
[figure not shown]
Flow diagram of the research process

Subjects will be recruited from three level III NICUs in Shenzhen, Guangdong Province, China: 1) Shenzhen People's Hospital (about 6000 births in 2021 and a preterm birth rate of about 11%), 2) Longgang Maternal and Child Health Hospital (about 13,000 births in 2021 and a preterm birth rate of about 6.7%), and 3) Bao’an Maternal and Child Health Hospital (about 18,000 births in 2021 and preterm birth rate of about 7%). Shenzhen People’s Hospital designed and initiated the study. It is the coordinating center and the affiliation of the sponsor (ZY). These three NICUs are all located in economically developed areas in China, provide prenatal care, delivery, postnatal care, neonatal treatment and other services.

### Inclusion/exclusion criteria

Inclusion criteria: 1. gestational age less than 32 weeks and birth weight less than 1500 g; 2. admission to NICU ≤ 24 h; and 3. be able to start the agreement within 72 h of birth.

Exclusion criteria: 1. birth asphyxia (defined as umbilical artery / first hour arterial PH < 7.0 or cardiopulmonary resuscitation in the delivery room); 2. birth complicated by severe gastrointestinal malformations (such as intestinal atresia, esophago-tracheal fistula, intestinal rotation abnormalities, congenital megacolon); 3. prenatal diagnosis of congenital chromosomal abnormalities or suspected congenital genetic metabolic diseases; and 4. maternal drug abuse or contraindications to breastfeeding (HIV and cytomegalovirus infection).

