### Collection of milk and oropharyngeal administration procedure

Obstetric nurses will encourage the mother of each newborn to start lactation within 24 h of delivery and educate them on breast massage and electric breast suction every 3 h. Mothers of preterm infants will be encouraged to milk frequently with hygienic hands to ensure a steady supply of breast milk. To ensure the feasibility of oropharyngeal administration of mother’s milk to preterm infants in the treatment group, the mother’s milk will be collected in a pre-labeled sterile milk collection bag. A minimum colostrum volume of 1.6 ml will be collected and stored in the breast milk refrigerator of NICU. After ascertaining that baby's information is consistent with details in the label on the breast milk storage bag, an on-site investigator (nurses preparing syringes) will select the storage bag with the latest lactation time and use sterile gloves and syringes to suck 0.1 ml of colostrum or sterile water for oropharyngeal administration, and cover them with opaque tape and needle cap. Each syringe will be labeled with serial number, hospitalization number, name and date. Then, the bag will be stored at 0 ~ 4℃ for 24 h for subsequent intervention. In this study, all other storage bags will be stored in a freezer at -18 °C until the infant begins enteral feeding.

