In the first 48–72 h the treatment group will receive the treatment measures: two 1 mL sterile syringes each aspirated with 0.1 mL of colostrum, placed at room temperature for 5 min. The colostrum will be maintained at room temperature for OAC use. After removing the tip and cap of the first syringe, the colostrum will be slowly injected along the right oral mucosa for at least 20 s. Then, the right buccal mucosa will be wiped with a sterile cotton swab for at least 10 s. The second syringe will be used in the same way on the left oral mucosa. The procedure will be performed every three hours for five days. The control group will be treated with sterile water following similar operation steps. Colostrum for the control group will be frozen in the NICU breast milk refrigerator for enteral feeding. Vital signs will be monitored throughout the process, including heart rate, respiration, body temperature and pulse oxygen saturation. During treatment, newborns will be regularly monitored and observed. If their clinical symptoms are unstable (heart rate is greater than 200 or less than 100, breathing is greater than 80, or the oxygen saturation is maintained above 85% only when the oxygen concentration increases by 10%) [44], the intervention will be interrupted. Once the clinical situation stabilizes, the treatment will be resumed immediately, and the final intervention dose and adverse reactions recorded.

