### Participant recruitment and informed consent

Data collection will begin in October 2022 and is expected to end in September 2023. Shenzhen People’s Hospital is the pilot research unit, and the pilot research will be carried out from August to September 2022. The annual census of very preterm infants in this facility is relatively high and the breastfeeding rate is very high (above 80%), hence ideal for the recruitment of subjects. Mothers who meet the inclusion criteria (fetal weight < 1500 g estimated by ultrasound) will be invited to participate. To achieve full registration of participants and target sample size, breast-feeding education will be provided in obstetrics to improve lactation awareness. Professional staff will guide pregnant women and provide them with breast care (such as breast massage). The principal investigator (PI) will explain the study in detail and respond to any questions raised. Mothers will be informed of their right to withdraw from the intervention at any time. They will also be informed that if they decline to participate in the study, their care and that of their infants will not be affected.

Written informed consent will be obtained from the patient's guardian. This study complies with the Declaration of Helsinki.

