### Randomization

A 1:1 block randomization scheme will be adopted. Each group will be stratified by birth gestational age (< 28 weeks, 28 weeks, and 32 weeks). A random serial number will be randomly generated for each layer using SAS (v9.4 SAS Inst. Inc., Cary, NC) before the start of the study. The block length will be 6. Statisticians will prepare sealed, numbered, opaque envelopes for each site and hand them over to the study coordinator, who will ensure that the envelopes are used in a numerical order. After receiving the notice, the study coordinator will open the envelope, take down the group assignment form, copy the form and send it to the statistician. The manuscript will be left in the case file of the preterm infant. To achieve blinding, the study coordinator preparing the syringe (colostrum or placebo) will be different from the nurse conducting the intervention. The subjects, intervention nurses, the principal investigator and the data verifier will be blinded. During the pilot test, non-fixed codes will be used for blinding to represent each allocation scheme to prevent unblinding by inadvertently losing blindness to all trial participants.

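### Nothing requires mother's colostrum to be available before allocation, so lack of milk can leave an infant untreated, or counted as lost, in the OAC arm only

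*Protocol article*

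**What the plan says.** All references are to the Protocol article.

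- **Who is randomised.** Study design: "Infants who meet these inclusion criteria will be randomly divided into two groups in a ratio of 1:1".
- **Eligibility.** Inclusion/exclusion criteria lists three inclusion items: gestational age with birth weight, early NICU admission, and "be able to start the agreement within 72 h of birth". None mentions milk supply. The only related item excludes contraindications to breastfeeding.
- **Allocation.** Randomization: "After receiving the notice, the study coordinator will open the envelope". What the notice certifies is not stated.
- **Milk.** Collection of milk and oropharyngeal administration procedure gives the purpose of collection as "To ensure the feasibility of oropharyngeal administration of" mother's milk in the treatment group, and then: "A minimum colostrum volume of 1.6 ml will be collected and stored in the breast milk refrigerator of NICU". No deadline is set, and the minimum is not tied to randomisation.
- **Control arm.** Same section: "The control group will be treated with sterile water following similar operation steps". Control mothers' colostrum is also collected, and is frozen for enteral feeding.
- **Analysis.** Statistical analysis specifies intention to treat. Missing data counts an infant receiving less than 70% of the expected dose as a follow-up loss.
- **Supply.** Participant recruitment and informed consent says of the coordinating site that "the breastfeeding rate is very high (above 80%), hence ideal for the recruitment of subjects". No figure is given for the other two sites.

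**The concern.** Only the OAC arm needs the mother's milk in order to start; the control arm needs sterile water. If milk is not checked before allocation, its absence acts after allocation, and in one arm only.

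An OAC infant without milk can then be handled in two ways, and the article supports each in a different section:

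- **Kept under intention to treat.** The comparison stays unbiased as an effect of assignment, but it is diluted and the trial loses power.
- **Counted as lost under the 70% rule.** The OAC arm then holds only infants whose mothers produced milk, while the control arm holds both kinds. The Discussion itself says that feeding type shifts the gut microbiota, so the arms would differ on a cause of the primary outcome for a reason other than OAC.

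**Working it through.** **1. The plan's own figure.** Sample size assumes a Shannon difference of 0.2, SD 0.6, two-sided 0.05 and 80% power.

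- n per arm = 2 × (1.96 + 0.8416)² × 0.6² / 0.2² = 141.3, so 142 by the normal approximation. The two-sample t-test gives 142.2, so 143. The stated 143 reproduces.
- 143 / (1 − 0.10) = 158.9, so 159; 143 / (1 − 0.12) = 162.5, so 163. The stated 160 corresponds to a loss of about 10.6%.

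**2. What the milk minimum covers.** Dosing every 3 h is 8 doses a day, so 8 × 0.2 ml = 1.6 ml, exactly one day. Five days are 40 doses, or 8.0 ml. The 70% rule is 0.7 × 40 = 28 doses, or 5.6 ml. An OAC infant with no milk receives 0 of 40 doses and falls under the rule. The same infant given water can receive all 40.

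**3. Size.** Let f be the share of mothers with no usable colostrum. The documents do not give it; **f = 5–20% is an assumption**. Common loss is taken as 10%, so n = 160 × 0.90 = 144 per arm.

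*Kept, with no effect in untreated infants.* Difference = 0.20 × (1 − f). Power = Φ(difference × √(n/2) / 0.6 − 1.96).

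- f = 0: 0.20 × 8.485 / 0.6 − 1.96 = 0.868, power 81%.
- f = 20%: 0.16 × 8.485 / 0.6 − 1.96 = 0.303, power 62%.

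*Dropped from OAC.* OAC n = 144 × (1 − f). SE = 0.6 × √(1/144 + 1/n_OAC). Power = Φ(0.20/SE − 1.96).

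- f = 20%: n_OAC = 115.2, SE = 0.075, 2.667 − 1.96 = 0.707, power 76%.

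| f | Infants of 160 | Kept: difference | Kept: power | Kept: evaluable per arm for 80% | Dropped: OAC vs control | Dropped: power |
|---|---|---|---|---|---|---|
| 5% | 8 | 0.19 | 77% | 157 | 137 vs 144 | 80% |
| 10% | 16 | 0.18 | 72% | 175 | 130 vs 144 | 79% |
| 15% | 24 | 0.17 | 67% | 196 | 122 vs 144 | 77% |
| 20% | 32 | 0.16 | 62% | 221 | 115 vs 144 | 76% |

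With 12% common loss the kept-branch power runs from 80% at f = 0 to 76–61% over f = 5–20%.

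**4. Bias in the dropped branch.** The control mean contains a share f of infants without mother's milk and the OAC mean contains none, so bias = f × D, where D is the Shannon gap between infants with and without milk. D is not given for this contrast. Sample size quotes day-7 differences of 0.2–0.6 between feeding types; borrowing that range as an assumption:

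- f = 5%: 0.01 to 0.03.
- f = 20%: 0.04 to 0.12, against a target of 0.20.

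The documents do not settle the sign of D.

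**The case against.** **The criterion is not failed by arm.** A reader might infer that the same infant is eligible if allocated to water and ineligible if allocated to OAC. The documents do not support that. The 72 h item is an inclusion criterion, only infants who meet the criteria are randomised, and allocation is concealed in opaque envelopes, so it is judged before the arm is known. A site could sensibly read it as able to start either arm, which includes having milk. Then there is no imbalance. That part of the objection stands. What remains is that the text does not say so, and three sites may read it differently.

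**Supply is partly addressed.** Every mother is encouraged to start lactation within 24 h and to express every 3 h, dosing starts at 48–72 h, and milk is collected in both arms. This makes a shortage less likely but does not make milk a condition of allocation.

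**An article condenses.** What the notice certifies may be set out in the full protocol or in the flow diagram, which is not shown. This is a fair caution. Yet the article does print numbered criteria and a step-by-step allocation procedure, and whether the experimental material must exist belongs among them.

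**Bias needs removal after randomisation.** Correct. Under intention to treat the result is ordinary non-adherence. The selection arises only if the 70% rule removes infants from the analysis, which is in tension with the stated analysis set but is not ruled out.

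**The size is assumed.** Also correct. The rate above 80% is for breastfeeding at one hospital, not for colostrum by 72 h. The planned 10–12% loss may already include some under-dosing, so the dropped-branch counts may double count. Even so, power there stays at 76–80%; the problem in that branch is selection, not power.

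**Conclusion.** The gap is real and should be closed. No eligibility or allocation step makes mother's colostrum a condition of opening the envelope, and only the OAC arm depends on it. Followed as written, the plan can randomise an infant who cannot receive the experimental treatment. That infant then either dilutes the contrast or is counted as lost, in one arm only.

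The plan does not say that infants are randomised without milk, nor that eligibility differs by arm; neither should be read into it.

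The size rests on an assumed 5–20% of mothers without milk, zero effect in untreated infants and 10% common loss. On those terms, keeping the infants costs 4 to 19 percentage points of power (81% to 77–62%). Dropping them costs little power but introduces a bias of about 0.01–0.12 Shannon units, if the gap between infants with and without milk resembles the feeding-type differences quoted in the Sample size section. If almost all mothers have milk by 72 h, both effects become negligible.

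**What to change.** 1. In Inclusion/exclusion criteria and in Randomization, state that for every infant, before the arm is known, the existing 1.6 ml minimum of own-mother colostrum is confirmed in the NICU before the envelope is opened, within the existing 72 h limit.
2. Because 1.6 ml is one day's supply out of 8.0 ml, this prevents failure to start but not a later shortfall. Reconcile Missing data with Statistical analysis so that infants under-dosed for lack of milk stay in the intention-to-treat analysis with their stool results. The 70% threshold can still define a separate per-protocol set.

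No dose or schedule changes.

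**Cost.** The change needs protocol wording and one check before opening the envelope; milk is already collected in both arms. Accrual slows: 320 randomised infants would need 320 / 0.95 = 337 otherwise eligible infants at an assumed 5% without milk, and 320 / 0.80 = 400 at 20%, within a planned one-year recruitment. The population narrows to infants whose mothers have early milk, who are the only ones able to receive OAC. The trial is already recruiting, so the check protects only infants not yet randomised; the second step covers all of them.
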